### 2.9. Discontinuation of the Intervention

The intervention will be terminated in cases with severe adverse events, when participants wish to withdraw from the trial, or when patients use unpermitted medication that would interfere with the recovery outcomes. Patients will have the option to ask the doctor about possible alternative therapies (e.g., nutritional support such as use of tricreatine *β*-hydroxyl-methylbutyrate, antioxidant therapy, and immunoglobulin therapy).

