### 2.13. Safety Assessment

Adverse events (AEs) are defined as events in which at least four participants suffer from the same symptom, including any undesirable experiences that may occur during the trial period. This may or may not be associated with the intervention. Participants will be instructed to report any AE to the research team at any time. All details of AE, including the time of occurrence, description of symptoms, duration of symptoms, severity, management measures, and causality to the intervention, will be recorded on case report forms (CRFs). The common AEs related to acupuncture, including local skin pain, itching, ulcers, leaving needles in participants, nausea during acupuncture, fainting during acupuncture, severe sharp pain, sharp pain lasting for more than 30 min, hematomas around the site of needling, bleeding, numbness, infection around the needle sites, sleeplessness after acupuncture, and dizziness after acupuncture, will be reported [20]. The causality between AEs and intervention will be assessed according to the World's Health Organization Uppsala Monitoring Center System for Standardized Case Causality Assessment [21]. In the event of AE occurrence, patients will be given an appropriate treatment until their conditions stabilize. Severe AEs will be reported to the safety monitoring board within 24 h.

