### 2.16. Data Collection and Management

The study staff will be responsible for the collection of baseline characteristic data and medical results during the screening period. All participants' scores, observation times, AE records, and safety assessments will be consolidated in a single CRF. CRFs will be filled out immediately and accurately. Outcome evaluators will examine the outcomes at the baseline (before the treatment), 2 weeks (during the treatment), 4 weeks (end of treatment), and 3 months after last treatment (during the follow-up period). Data monitoring and management will be performed every 3 months by the Clinical Research Center of the Shanghai General Hospital affiliated to the Shanghai Jiaotong University. The clinical research monitors will monitor the medical practitioners to ensure that all processes are implemented correctly. A data monitoring committee (DMC) independent of the sponsor and with no conflicts of interest will be responsible for monitoring the progression of the trial and ensuring patient safety. Interim analyses and trial discontinuation plans will not been specified, but will be provided upon DMC's request. Two assistants will enter all the data in an electronic database based on double data entry. The statistical manager will be responsible for data organization, coding, range checks for data values, and data conversion for quality control. The database will be locked after cleaning all data. If any participant withdraws from the trial, detailed reasons will be collected, and the rate of withdrawal will be analyzed statistically.

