### 2.22. Safety Analysis

According to the definition of AEs, AEs will be recorded in conjunction with their severity level, causes, and explanations. Moreover, the number and the rate of AE will be described statistically. If AEs would be required to be compared between groups, the *χ*^2^ test or the Fisher's exact test will be used for statistical analyses.

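### The 24-hour safety report is keyed to severe rather than serious adverse events, so a serious event not graded severe has no stated reporting time, and the receiving board is not linked to the DMC

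*Protocol article*

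**What the plan says.** Section 2.13 of the protocol article gives the one expedited rule in the document: "Severe AEs will be reported to the safety monitoring board within 24 h". Among the details to be entered on the case report form, the same section lists "description of symptoms, duration of symptoms, severity, management measures, and causality to the intervention". Section 2.22 carries the attribute into the analysis: "AEs will be recorded in conjunction with their severity level, causes, and explanations". Section 2.13 also opens with an unusual definition: "Adverse events (AEs) are defined as events in which at least four participants suffer from the same symptom".

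Oversight is described in three places. Section 2.13 names a safety monitoring board. Section 2.16 sets up an independent DMC that "will be responsible for monitoring the progression of the trial and ensuring patient safety". Section 2.17 adds an advisory board. Nothing states how the three relate to one another.

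**The concern.** Severity and seriousness are different attributes. Severity is how intense an event is. Seriousness, in the sense usual in trials, is what the event leads to: death, threat to life, a longer ICU or hospital stay, or lasting disability. Expedited reporting exists to bring events with such consequences quickly to people who can judge the trial as a whole. A rule keyed to intensity can send a painful but harmless event within 24 hours and leave out a less intense one with lasting consequences.

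The distinction matters in this population. Participants are mechanically ventilated (section 2.2.1), and section 2.5 provides for some in coma or under continuous sedation. Intensity of symptoms is hard to grade in such patients, and they cannot report events themselves. Consequences can be judged from the clinical course.

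The recipient is also uncertain. Staff working to a 24-hour clock need one identified body, and the only body the document charges with patient safety is not the one named in the rule.

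**Working it through.** The article states no figure for this point, so the check sets the sections side by side.

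1. **What severe means in the document.** In 2.13 severity is a recorded item, listed apart from management and causality. The list of common acupuncture events in the same section uses the word for the intensity of pain. Section 2.22 speaks of a severity level. These uses all point to intensity. No grading scale is defined.

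2. **Whether seriousness appears.** The article neither uses nor defines serious adverse event as a category. It gives no criterion based on death, threat to life, prolonged stay or disability.

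3. **What the rule reaches.** Applying 2.13 as worded, and setting the four-participant definition aside for the moment:

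| Illustrative event | Severe? | Serious? | 24-hour report? |
|---|---|---|---|
| Needle pain graded severe that resolves without consequence | yes | no | yes |
| Needle-site infection of moderate intensity that prolongs the ICU stay | no | yes | no stated time |
| Event graded severe that threatens life | yes | yes | yes |

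The second row is the gap. Infection around the needle site is on the article's own list of expected events.

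4. **The definition beneath the rule.** An adverse event needs at least four participants with the same symptom. Read literally, an event seen in one, two or three participants is not an adverse event, so it cannot be a severe one and triggers nothing. With 56 participants planned, 28 per arm, up to 3/56 = 5.4% of the trial could have the same event below the threshold, or 3/28 = 10.7% of an arm if all three were in one arm. Replacing severe with serious would not close the gap while this definition governs the rule. The single infection in the table would still not qualify.

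5. **The recipient.** The safety monitoring board occurs only in 2.13. The patient-safety task sits with the DMC in 2.16. No sentence says that they are the same body, or that one passes reports to the other.

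6. **What else might set a reporting time.** Section 2.16 says "Data monitoring and management will be performed every 3 months", but this is an activity of the hospital's Clinical Research Center. Section 2.17 adds monthly external monitoring by a team from that Center. Neither is described as a safety review by the board or the DMC, and no DMC meeting interval is given. A serious event not graded severe therefore has no stated deadline of any length.

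**The case against.** The strongest reply is that severe is loose wording for serious. Section 2.9 says "The intervention will be terminated in cases with severe adverse events", and section 2.2.3 uses the word for life events that force withdrawal. Both read more like categories of consequence than grades. This may be what was meant. But neither section defines the term, and 2.13 itself uses it for intensity, so the wording needs correcting under either reading.

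A second reply is that seriousness criteria, form items and a DMC's remit belong in the full protocol, which section 2.24 says is available on request. That is fair for what the article leaves out. It does not cover a rule that the article states in full and ties to the wrong attribute.

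A third is that the two bodies may be one under two names. That may be so. This part is a naming point to reconcile and does not show a broken reporting line.

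Section 2.8 also provides continuous nursing and a physician examination every 6 hours. Events would be seen and treated at the bedside. That is clinical care, not independent review of the trial, so it narrows the consequence without removing it.

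A reader might go further and infer three things that the documents do not support:

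- **That such an event waits for a 3-monthly safety review.** The 3-monthly activity is data monitoring and management, and monthly monitoring is stated as well. For the same reason, a count of participants treated per 3-month cycle would measure nothing relevant.
- **That seriousness is never recorded.** The list of details in 2.13 is open-ended, so an item's absence from it does not show that the form lacks it. Section 2.12 collects 28-day survival, which captures deaths to that point.
- **That serious events could not be reported by arm.** This falls with the previous inference.

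**Conclusion.** The point holds in a limited form. The only expedited rule in the article is keyed to an intensity attribute, no seriousness criterion is given, and a serious event not graded severe has no stated reporting time. The recipient is not linked to the DMC. The four-participant definition, read literally, would also keep an isolated event out of the rule.

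The conclusion assumes that severe carries in the 24-hour rule the meaning it has elsewhere in 2.13 and in 2.22, and that nothing outside the article overrides the rule. If the sponsor meant serious, the defect is one of wording, but the correction is the same. The point does not bear on power, the significance level or the primary comparison. It should be corrected because it concerns participant safety and the change is cheap.

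**What to change.** In section 2.13:

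- Key the 24-hour report to serious adverse events of any severity grade, with the seriousness criteria stated.
- State that the rule applies to an event in any single participant and is not subject to the four-participant definition.
- Add seriousness to the listed adverse event items, separate from severity.
- Name the DMC of section 2.16 as recipient, or state that the safety monitoring board and the DMC are the same body.

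In section 2.22, report serious adverse events by arm.

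Sections 2.9 and 2.2.3 use the same word. The sponsor should say what it means there, so that the terms agree across the document.

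The cost is a few sentences and one tick-box on the adverse event form. No treatment, endpoint or sample size changes. The small downside is more 24-hour reports, because consequences such as prolonged stay are common in ICU patients.

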### 2.14. Follow-Up

The health statuses of the participants after the 4-week treatment period will be followed up on a monthly basis via telephonic and message communications for 3 months based on the previous study for this disease [22]. The symptoms and medication compliance or changes in medication will be recorded. In the event that participants withdrew from the trial or deviated from the intervention protocols, the staff will record the reasons for their withdrawal and the details of their new medications as well as the latest outcome data including the symptoms and frequency of the attacks prior to their exclusion from the study.

### 2.15. Participant Timeline

An overview of the recruitment timeline, interventions, and all time points of participant evaluation is summarized in Figure 2.

### 2.16. Data Collection and Management

The study staff will be responsible for the collection of baseline characteristic data and medical results during the screening period. All participants' scores, observation times, AE records, and safety assessments will be consolidated in a single CRF. CRFs will be filled out immediately and accurately. Outcome evaluators will examine the outcomes at the baseline (before the treatment), 2 weeks (during the treatment), 4 weeks (end of treatment), and 3 months after last treatment (during the follow-up period). Data monitoring and management will be performed every 3 months by the Clinical Research Center of the Shanghai General Hospital affiliated to the Shanghai Jiaotong University. The clinical research monitors will monitor the medical practitioners to ensure that all processes are implemented correctly. A data monitoring committee (DMC) independent of the sponsor and with no conflicts of interest will be responsible for monitoring the progression of the trial and ensuring patient safety. Interim analyses and trial discontinuation plans will not been specified, but will be provided upon DMC's request. Two assistants will enter all the data in an electronic database based on double data entry. The statistical manager will be responsible for data organization, coding, range checks for data values, and data conversion for quality control. The database will be locked after cleaning all data. If any participant withdraws from the trial, detailed reasons will be collected, and the rate of withdrawal will be analyzed statistically.

### 2.17. Quality Control

All the staff involved in the study, including acupuncturists, rehabilitation therapists, ultrasound examination doctors, operational assistants, and nurses, will be obliged to receive advanced training on filling out CRFs, conducting blood tests, details of acupuncture and rehabilitation therapy, scales and ultrasound examinations, and follow-up visit skills. All the staff members will be asked to take exams after training to ensure strict adherence to the study protocol and consistency of the trial administration processing, including acupuncture, rehabilitation therapy, and evaluation methods. All the staff members will be provided with a written protocol and standard operation procedure documents. All acupuncturists have acquired acupuncture licenses from the Ministry of Health of People's Republic of China; they must have a clinical experience of >5 years. To improve the quality of study reporting and conduct, we will develop a standard operating procedure manual according to the principles of the Consolidated Standards of Reporting Trials Extension for Chinese Herbal Medicine Formulas [23]; it will be explained to all the investigators. Intervention details, such as acpuncture rationale, details of needling, treatment regimen, time selection, practitioner background and confidence, and adequacy of stimulation, will be extracted and evaluated according to STRICTA [24]. To ensure the authenticity of the data, a special research team from the Clinical Research Center of the Shanghai General Hospital, which is affiliated to the Shanghai Jiaotong University and independent of the investigators and sponsors, will externally monitor the study in the hospital on a monthly basis. An advisory board will monitor the trial and provide advice when necessary. To improve adherence to the intervention, free 4-week treatments and examinations will be provided. To ensure that treatment and follow-up run as scheduled, participants will be given monetary compensation at the end of the follow-up period.

### 2.18. Statistical Analysis

#### 2.18.1. Sample Size Calculation

The trial will test two groups in parallel. The sample size calculation will be performed using the software SAS (version 9.3, SAS Institute Inc., Cary, NC, USA). The mean change in the primary outcome before and after treatment will be used as the indicator of efficacy evaluation in the calculation of the sample size. The results of previous studies yielded a mean ultrasound measurement of muscle thickness change of 0.45 ± 0.1 [25] and a mean ultrasonic intensity of muscle change of 25 ± 3 [26] after the loss of muscle mass and function. To detect a significant difference with a power of 80%, an alpha value of 0.05, and an acceptable delta value of 0.2, a sample size comprising at least 23 participants in each group will be needed. We have added an additional five patients per group considering a possible 20% dropout.

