In this study, we proposed the use of muscular ultrasonography to evaluate the muscle strength by visualizing the muscle's cross-sectional area, layer thickness, and echo intensity based on the grayscale and penetration angle [41]. This is because the ultrasonic measurement of muscle thickness can be used to assess the presence of sarcopenia, and the echo intensity can be associated with muscle strength and correlated with the risk of frailty in elderly outpatients [25, 26]. We believe that muscle ultrasound can reliably detect the pathological changes of ICUAW [41]. Our study will address whether this treatment will affect the quadriceps femoris muscle area, thickness, vastus intermediate muscle thickness, subcutaneous tissue thickness, ultrasonic intensity of the rectus femoris, and MBI and MRC total scores in the long term after the last treatment.

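### The stated inputs do not reproduce 23 per group, so the 80% power figure is unsupported; this alone does not show that the trial is underpowered

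*Protocol article*

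**What the plan says.** Section 2.18.1 of the protocol article bases the calculation on the mean change in the primary outcome before and after treatment. It takes two results from previous studies: a thickness change of 0.45 with SD 0.1, and "a mean ultrasonic intensity of muscle change of 25 ± 3". No units are given for either. It then states the target: "To detect a significant difference with a power of 80%, an alpha value of 0.05, and an acceptable delta value of 0.2". The result is at least 23 participants per group. For losses it says: "We have added an additional five patients per group considering a possible 20% dropout". This gives the 28 per group, 56 in total, of the Abstract.

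The section does not say whether the test is one- or two-sided, which outcome the 0.2 refers to, or whether 0.2 is absolute, standardised or relative. Section 2.21 names the t-test for comparing two groups when the data are normally distributed, and a mixed-effect model for the ultrasound data.

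**The concern.** The paragraph gives a power, an alpha, a delta, two SDs and a result, so it can be checked. The SDs differ by a factor of 30 (3 / 0.1), so a single unitless delta cannot mean the same for both outcomes. If no reading of the inputs leads to 23, the stated power belongs to no difference that the protocol names, and a reader cannot tell what effect 56 patients were meant to detect. The dropout step also appears to inflate by multiplying by 1.2 instead of dividing by 0.8.

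**Working it through.** **Inputs (section 2.18.1).** Power 80%; alpha 0.05; delta 0.2; SD 0.1 (thickness, mean change 0.45); SD 3 (intensity, mean change 25); result 23 per group; 5 added per group for 20% dropout. Allocation is 1:1 (section 2.2.5). Assumption: a two-sided test, since sidedness is not stated; one-sided results are also shown.

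**Method.** With d = delta/SD, the normal approximation is n per group = 2 × (1.960 + 0.842)² / d². The t-test figure is the smallest n for which the noncentral t distribution, with 2n − 2 degrees of freedom and noncentrality d × √(n/2), gives at least 80% power.

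**Step 1. Try to reproduce 23.**

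| Reading of 0.2 | d | n, normal approx. | n, t-test | n, one-sided t-test | Power at 23 (two-sided t-test) |
|---|---|---|---|---|---|
| Absolute, SD 0.1 | 0.2/0.1 = 2.0 | 3.9, so 4 | 6 | 4 | above 99.9% |
| Absolute, SD 3 | 0.2/3 = 0.067 | 3,532 | 3,533 | 2,783 | 5.6% |
| Standardised effect | 0.2 | 392.4, so 393 | 394 | 310 | 10.2% |
| 20% of 0.45 = 0.09, SD 0.1 (not stated) | 0.9 | 19.4, so 20 | 21 | 16 | 84.7% |
| 20% of 25 = 5, SD 3 (not stated) | 1.67 | 5.7, so 6 | 7 | 6 | above 99.9% |

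In the first row, 5 per group gives 79.1% and 6 gives 87.6%, so 6 is the minimum. No row gives 23. Changing other inputs on the fourth row does not help: by the normal approximation, a Bonferroni alpha of 0.025 gives 24 and 90% power gives 26, and the text states neither. Multiplying the SD of 0.1 by √2 gives 9 per group for a delta of 0.2 and 40 for 0.09 (t-test).

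**Step 2. What 23 per group does detect.** Solving the t-test for d at n = 23 and 80% power gives d = 0.845. That is 0.845 × 0.1 = 0.084 on the thickness scale, or 0.845 × 3 = 2.5 on the intensity scale. For a delta of 0.2 to give 23, the SD would have to be 0.2/0.845 = 0.237, which appears nowhere in the document.

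**Step 3. Dropout.**
- Evaluable after 20% loss: 28 × 0.80 = 22.4, below the stated minimum of 23.
- Inflation that keeps 23: 23/0.80 = 28.75, so 29.
- The 28 fits 23 × 1.2 = 27.6, rounded up.
- Loss that 28 can absorb while keeping 23: 5/28 = 17.9%.
- If 23 per group gives 80% power (d = 0.845), 22 per group gives 78.1%. The difference detectable at 80% power with 22 per group is 0.865 SD.

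**The case against.** Read as 20% of the stated 0.45 thickness change, the delta is 0.09 with SD 0.1 and needs 21 per group. That is close to 23, and power would be 84.7% at 23 and 83.0% at 22, so the target would be met even after the assumed loss. This reading deserves to be disclosed, but it does not rescue the figure. The text calls 0.2 a delta, not a percentage; 21 is not 23; and the same reading gives 7 for intensity.

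A reader might infer that the trial is underpowered. The document does not support this. The plainest same-scale reading, 0.2 against SD 0.1, gives power far above target; only the other two literal readings give power far below it. A reader might also infer that a null result could not be interpreted. That goes too far, because the estimate and its confidence interval show which effects the data exclude, whatever the planning power was.

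The dropout slip is small. Section 2.21 plans an intention-to-treat analysis with a mixed-effect model, and section 2.23 plans for missing data, so patients who drop out need not leave the analysis altogether. The slip would not merit a major point alone.

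The Discussion cites the two source studies for sarcopenia and for frailty in elderly outpatients. That is a reason to ask whether their SDs apply to a 4-week change in ICU-acquired weakness, but the sources are not at hand and no fault is claimed. Nor is a separate calculation for each primary measure required of a condensed article.

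**Conclusion.** The point holds in this form: 23 per group for 80% power at alpha 0.05 does not follow from the stated inputs. The literal readings need 6, 394 or 3,533 per group by a two-sided t-test, and one-sided testing does not bring any of them to 23. The cause is that the 0.2 is tied to no outcome, unit or scale. For the same reason no single corrected sample size can be given, and the trial cannot be called underpowered or overpowered.

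The dropout allowance is a minor error of one patient per group (28 against 29), worth about 2 points of power at most if all who drop out are lost to the analysis.

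These figures assume equal groups, a common SD and a simple two-group comparison of change. A separate analysis plan cannot remove the conflict, because the inputs and the result both stand in the same published paragraph.

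**What to change.** Rewrite section 2.18.1 for one named primary outcome. Give the between-group difference with its unit or scale, the SD of the 4-week change with its source, and the sidedness. Remove "an acceptable delta value of 0.2", and do not back-fit an SD (such as 0.237) to arrive at 23.

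Keep enrolment at 28 per group and report what it delivers. Suggested wording: *28 patients per group will be randomised. With 20% loss, about 22 per group will be evaluable, which gives 80% power at two-sided 0.05 for a between-group difference in 4-week change of about 0.86 SD (0.845 SD with 23 per group).* Then give that difference in the outcome's units over a range of plausible SDs. With the article's own SDs it is 0.865 × 0.1 = 0.086 for thickness or 0.865 × 3 = 2.6 for intensity, and it grows in proportion to the SD.

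For dropout, either state the allowance as about 18%, or say that 22 evaluable patients per group are expected.

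The cost is one rewritten paragraph, with no change to enrolment or conduct. The downside is that the detectable effect becomes explicit and looks large, so the authors will have to say whether a difference of that size is realistic.
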